# Surgical vs. non-surgical management of displaced type-2 odontoid fractures in patients aged 75 years and older: study protocol for a randomised controlled trial

**DOI:** 10.1186/s13063-018-2690-8

**Published:** 2018-08-22

**Keywords:** Odontoid fractures, Elderly, Osteoporosis, Spinal fractures, Surgical treatment

## Abstract

**Background:**

Displaced odontoid fractures in the elderly are treated non-surgically with a cervical collar or surgically with C1–C2 fusion. Due to the paucity of evidence, the treatment decision is often left to the discretion of the expert surgeon.

**Methods:**

The Uppsala Study on Odontoid Fracture Treatment (USOFT) is a multicentre, open-label, randomised controlled superiority trial evaluating the clinical superiority of the surgical treatment of type-2 odontoid fractures, with a 1-year Neck Disability Index (NDI) as the primary endpoint. Fifty consecutive patients aged ≥ 75 years, with displaced type-2 odontoid fracture, are randomised to non-surgical or surgical treatment. Excluded are patients with an American Society of Anaesthesiologists (ASA) score ≥ 4, dementia nursing care or anatomical cervical anomalies.

The minimal clinically important difference of the NDI is 3.5 points. A minimum of 16 patients are needed in each group to test the superiority with 80% power. By considering a 1-year mortality forecast of 29%, up to 25 participants are recruited in each group.

The non-surgical group is fitted with a rigid cervical collar for 12 weeks. The surgical group is treated with a posterior C1–C2 fusion. All participants are monitored with regard to the NDI, EuroQol score (EQ-5D), socio-demographics and computed tomography (CT) at the time of injury, at 6 weeks, 3 months and 12 months. At 12 months, a dynamic radiographical investigation of upper cervical stability is performed.

The secondary endpoints are: EQ-5D score, activities of daily living (ADL), bony union, upper cervical stability and mortality.

**Discussion:**

USOFT is the first randomised controlled trial comparing non-surgical and surgical management of type-2 odontoid fractures in the elderly. Using the NDI and EQ-5D as endpoints, future value-based decisions may consider quality-adjusted life years gained. Major limitations are (1) the allocation bias of the open-label study design, (2) that only higher training levels of all core specialties of spine surgery are included in the surgical treatment arm and (3) that only one type of surgical stabilisation is investigated (posterior C1–C2 fusion), while other methods are not included in this study.

**Trial registration:**

ClinicalTrials.gov, NCT02789774. Registered retrospectively on 25 August 2015.

**Electronic supplementary material:**

The online version of this article (10.1186/s13063-018-2690-8) contains supplementary material, which is available to authorized users.

## Background

### Background and rationale

Unstable injuries to the upper cervical spine are a hazard to every elderly person, since associated dysphagia and respiratory restrictions are potential deadly complications [1]. The most common upper cervical fracture in elderly people aged ≥ 70 years is the type-2 odontoid fracture, with an incidence of 15.6 per 100,000 person-years in 2014 [2]. As with other osseous injuries in the elderly, the occurrence of odontoid fractures has been related to fragility, osteoporosis and falls [3]. The mortality of odontoid fractures, meanwhile, is strongly related to age, gender, comorbidity and type of treatment [4].

The treatment of displaced type-2 odontoid fractures in the elderly varies from external orthosis treatment with a rigid collar to surgery, including anterior screw osteosynthesis and posterior C1–C2 fusion. Some earlier non-randomised studies have shown no significant difference between surgical treatment or non-surgical treatment regarding functional outcome (NDI, Neck Disability Index) or functional outcome score), pain and patient satisfaction [5, 6] the AOSpine North America Geriatric Odontoid Fracture (GOF) study has found significantly better outcomes measuring the NDI and the SF-36 Bodily Pain dimension comparing non-surgically and surgically treated patients [7]. Despite the fatal implications of inaccurate treatment, the most recent treatment recommendations vary widely, while surgeon adherence is highly dependent on regional differences [8]. There is a trend towards non-surgical treatment in Sweden; the fear of overtreatment could be a contributing factor. Patient comorbidity could be another explanation for physicians’ tendency to use a cervical collar in the belief that this will avoid further damage. It could also be the tradition of the clinic that determines what treatment the patient should receive.

### Evidence

On 30 October 2017, a search in PubMed was performed with the search term “odontoid[Title] OR dens[Title] AND fracture[title]”. Of the 321 search results published between 1985 and 2017, only two prospective study were identified [7, 9, 10]. In the first prospective observational study, on percutaneous transarticular atlantoaxial screw fixation, 20 consecutive, multimorbid patients aged > 65 years with a type-2 odontoid fracture were included and followed for a minimum of 18 months [9]. The results from the study showed 88% healing of the fracture and 15% mortality within 3 months. In the other study 159 patients with a type-2 odontoid fracture were included in a multicentre prospective study, comparing surgical (*n* = 101) and non-surgical (*n* = 58) treatment. Treatment choice was determined by the physician and/or the patient. The subjects were followed at 6 and 12 months with outcome measures, including the Neck Disability Index (NDI) and Short Form-36v2 (SF-36v2). They found that the functional outcome was significantly better in the surgically treated patients [7].

There were three ongoing prospective studies (including USOFT) registered at the ClinicalTrials.gov database (status: recruiting, NCT02281994, NCT02800278, NCT02789774). Meta-analyses of the survival from type-2 odontoid fractures among the elderly aged ≥ 65 years report better survival for patients who are treated surgically (Hazard ratio (HR) = 0.64) [4], while this seems to diminish if only those aged ≥ 80 years are included [11]. Due to the retrospective nature of most published studies, considerable reporting and selection bias must be assumed, meaning that the strength of current treatment recommendations is questionable.

### Implications of this study

Previously published and ongoing studies are focussed on non-union and mortality in relation to different treatment modalities. Nowadays, value-based care requires health-related quality of life (HRQoL) measures to influence health policy and decision-makers. By studying HRQoL and the function of patients with type-2 odontoid fractures, while comparing non-surgical treatment and the most common surgical treatment (posterior C1–C2 fusion), we can address the cost-effectiveness of the treatment options.

## Methods

### Study aims and objectives

#### Primary objective

The primary objective is to compare neck disability at 1 year after non-surgical treatment with surgical treatment of displaced type-2 odontoid fractures.

#### Secondary objective

The secondary objectives are to compare the cost-effectiveness, the mortality, the HRQoL and the bony union of non-surgical with surgical treatment after 1 year.

#### Trial design

The Uppsala Study on Odontoid Fracture Treatment (USOFT) is a multicentre, open-label, randomised controlled superiority trial. The protocol follows the Standard Protocol Items: Recommendations for Interventional Trials (SPIRIT) Statement for clinical trial reporting (Additional file 1) [12].

### Study setting

The USOFT is being conducted in five departments of orthopaedic surgery in three university hospitals (Uppsala University Hospital, Malmö University Hospital and Karolinska University Hospital Stockholm) in Sweden. Participating university hospitals are level 1 trauma centres. All treating spine surgeons are orthopaedic or neurosurgical specialists with different levels of clinical experience in treating upper cervical spinal conditions.

### Eligibility criteria

#### Inclusion criteria

Patients are eligible for inclusion in this study if they meet all of the following criteria:Acute displaced odontoid fracture, type 2 [13]▪ Displacement is measured on a multiplanar reconstruction of a cervical spine CT scan and defined as a 5-mm anterior translator displacement, any posterior translator displacement or 10° of angulation [14–17]Age: 75 years or older

#### Exclusion criteria

Patients are not included in this study if they meet one or more of the following criteria:ASA class 4 or higher [18, 19]Severe dementia▪ Defined as being admitted to a nursing home or hospital because of dementiaAnatomical anomalies (i.e. occipitocervical assimilation)Injuries (i.e. spinal cord injury (SCI) or severe dislocation threatening SCI) that mandate surgery

### Interventions

#### Concomitant treatment in both groups

Collar in emergency department (Stifneck, Laerdal Medical, Stockholm Sweden)Pain medication (bolus: 2–5 mg morphine by the intravenous (IV) route)Diagnostic workupBaseline data collection according to Fig. 2Expertise of participating physicians: beginner (residents) to expert (consultant)Follow-up after 6 weeks, 3 months and 1 year, according to Fig. 2

#### Non-surgical treatment

The patient will be provided with a well-fitted and rigid collar, such as the Philadelphia collar (Ossur, Sollentuna, Sweden) or the Aspen collar (Aspen Medical Collars, Irvine, CA, USA). The collar will be worn 24 h a day for 12 weeks. The collar may be removed for short periods of time for personal hygiene when the patient is supine in bed.

CT scans will be repeated after 1 week, 6 weeks and 3 months. In case of increasing fracture displacement, or symptomatic non-union, the fracture will be treated surgically with a posterior C1–C2 fusion. The crossover will be documented, but all data will be analysed according to the intention-to-treat (ITT) principle.

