#### Computer tomography

CT is the most reliable radiographic tool to classify and evaluate healing in relation to type-2 odontoid fractures [33]. Bony union is assessed by a radiologist, independently from the study. Healing is defined as ‘not visible fracture line’ or ‘bone bridging in fusion’.

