### Statistics

For statistical analysis, R version 3.4.1 (R Foundation for Statistical Computing, Vienna, Austria) will be used. The results will be presented according to the CONSORT Statement for non-pharmacological interventions [26]. The analysis will be performed by intention-to-treat (ITT), and sensitivity analyses will include a per-protocol analysis.

Missing values will be imputed using multiple imputation by use of chained equations as implemented in the R package “mice” with 20 iterations [40]. Details of the statistical analysis are listed in Table 1.

**Table 1 Tab1:** Variables, measures and methods of analysis

Variable/Outcomes	Hypothesis	Outcome measures	Methods of analysis
*Baseline data:*	There is no difference between the two groups	Gender, age, Katz ADL, CCI, nursing home/hospitalisation, smoking status	Absolute numbers, percentages for categorical variables and the minimum, maximum, mean, SD and quartiles for quantitative variables
*Primary:*			
Function	There is a clinically important difference between the two groups, with improvement comparing baseline data with data from 6 weeks, 12 weeks, and 1 year. Surgical treatment is hypothesised to be superior	NDI (0–100%) [continuous]	Student *t* test, chi-square, Mann-Whitney, Fisher’s exact test. Time-dependent differences between AUC
*Secondary:*			
Health-related quality of life	There is a clinically important difference between the two groups	EQ-5D [continuous]	Student *t* test, chi-square, Mann-Whitney, Fisher’s exact test Time-dependent differences between AUC
Pain	There is a clinically important difference between the two groups	VAS (0–100) [continuous]	Students *t* test, chi-square, Mann-Whitney, Fisher exact test Time-dependent differences between AUC
Non-union	The non-union rate is lower in the surgical group	Bone bridge in CT [binary], mobility on extension-flexion radiographs [binary],	Chi-square test
Mortality	The survival is greater in the surgical group	all-cause mortality [binary], time to death [continuous, censored]	Kaplan-Meier analysis, Cox regression models, additional subdistribution hazards approach
Osteoporosis	There is no difference between the two groups	The bone density is > 2.5 standard deviations below normal DXA T-score [binary]	Chi-square
*Subgroup analysis:*			
septuagenarians vs. octogenarians vs. nonagenarians	Treatment effect is diminished in nonagenarians		
Goel-Harms technique vs. Magerl technique	There is no difference between the two groups		

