#### Description of the patient groups at baseline

The baseline features of the patients will be described with descriptive statistics using absolute numbers (*n*) and percentages for categorical variables and the minimum, maximum, mean, SD and quartiles for quantitative variables. The number of patients crossing over to surgical treatment or dropping out from follow-up will be documented.

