### Non-union

A chi-squared test will be used to compare the non-union rate between the two groups.

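### A collar patient fused for symptomatic non-union counts as healed in the collar arm once the rescue fusion has bridged at 1 year, so the union comparison describes collar with rescue fusion and understates failure of the collar alone

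*Protocol article*

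**What the plan says.** Five statements in the protocol article together fix how a rescued collar patient is scored.

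- **Rescue rule** (Non-surgical treatment): "In case of increasing fracture displacement, or symptomatic non-union, the fracture will be treated surgically". The operation is a posterior C1–C2 fusion.
- **Analysis set** (same section): the crossover is recorded, but "all data will be analysed according to the intention-to-treat (ITT) principle".
- **Time point** (Secondary outcome measures): CT healing and flexion-extension stability are both assessed after 1 year.
- **Definition** (Computer tomography): "Healing is defined as ‘not visible fracture line’ or ‘bone bridging in fusion".
- **Test** (Non-union): "A chi-squared test will be used to compare the non-union rate between the two groups". The hypothesis in Table 1 is directional: "The non-union rate is lower in the surgical group".

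The Secondary objective section states the aim as comparing "the HRQoL and the bony union of non-surgical with surgical treatment after 1 year". On crossovers, the section on baseline description adds: "The number of patients crossing over to surgical treatment or dropping out from follow-up will be documented". Table 1 lists a per-protocol sensitivity analysis for all outcomes and does not say how rescued patients are handled in it.

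**The concern.** For most outcomes, keeping a crossover in the allocated arm is the right default. Union differs in one respect: the rescue is triggered by the outcome itself and can then erase it. A collar patient found to have a symptomatic non-union is fused. If the fusion bridges, that patient enters the 1-year table as a healed collar patient. The second non-union measure in Table 1, mobility on flexion-extension films, moves the same way, because a solidly fused segment is stable.

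A reader of the results will take the collar non-union rate as the rate at which collar treatment fails to unite the fracture. Under the written scoring it is a lower figure. At stake is the interpretation of a stated secondary objective: a real difference in union could look smaller than it is, or the collar could look better than it is. The more often the collar fails and is rescued, the larger the gap.

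**Working it through.** **The plan's own figures.** The article gives no rate, power or sample size for non-union. Its NDI sample size is needed only to fix the number of survivors.

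- Per arm, with a difference of 3.5 and an SD of 3.5: 2 × (1.96 + 0.84)² × (3.5/3.5)² = 15.7, so 16. This matches the Sample size section.
- Inflation for 29% mortality: 16/0.71 = 22.5, so 23; from the t-test size of 17, 17/0.71 = 23.9, so 24. The stated minimum is 24, and nothing here disputes it.
- Survivors at 1 year: 24 × 0.71 = 17.04, taken as 17 per arm.

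**Inputs for union.**

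| Symbol | Meaning | Value | Source |
|---|---|---|---|
| q | surgical non-union | 12% | assumed, from "The results from the study showed 88% healing of the fracture" (Evidence section, 20-patient series) |
| p | collar non-union without rescue | 40, 50, 60% | assumed; not in the article |
| s | share of collar non-unions rescued | 0, 10, 25, 50% | assumed; not in the article |
| b | share of rescues bridged on the 1-year CT | 88% or 50% | assumed; 50% because fusion after the 3-month CT leaves about nine months |

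**Formula.** Counted collar non-union = p(1 − bs). This is below p whenever b and s are both above zero. It treats every rescued patient as one who would still have been un-united at 1 year.

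**Example.** p = 50%, b = 88%, s = 25%: 0.50 × (1 − 0.88 × 0.25) = 0.50 × 0.78 = 39%. The difference from surgery is 27 points, against 38 with no rescue.

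**Power** by exact binomial enumeration, 17 per arm, q = 12%, two-sided 0.05:

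| p | b | s | Counted collar rate | Uncorrected chi-squared | Fisher's exact |
|---|---|---|---|---|---|
| 50% | any | 0 | 50% | 69% | 55% |
| 50% | 88% | 10% | 46% | 59% | 45% |
| 50% | 88% | 25% | 39% | 43% | 30% |
| 50% | 88% | 50% | 28% | 20% | 12% |
| 50% | 50% | 10% | 48% | 63% | 50% |
| 50% | 50% | 25% | 44% | 54% | 41% |
| 50% | 50% | 50% | 38% | 40% | 27% |

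With b = 88% and s = 0, 10, 25, 50%, uncorrected chi-squared power is 46, 37, 26, 12% at p = 40% and 87, 78, 62, 31% at p = 60%.

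**Same revised share in both arms.** If surgical failures were also revised in share s and bridged at the same 88%, power at p = 50% would be 69, 63, 53, 37%. The loss shrinks but does not vanish.

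**Does the per-protocol analysis repair it?** Rescue is directed by the protocol, so it may count as adherence, and then nothing changes. If rescued patients are dropped, known non-unions leave the data and the rate is p(1 − s)/(1 − ps). At p = 50%: 0.375/0.875 = 42.9% for s = 25%, and 0.25/0.75 = 33.3% for s = 50%. Neither recovers 50%.

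**The case against.** **The comparison as written is coherent.** The rescue rule is part of the non-surgical arm's definition, and the objective asks about union after 1 year. Collar with rescue if needed, analysed by intention to treat, is a legitimate treatment-policy comparison. This stands. A reader might infer that the intention-to-treat result is wrong; the documents do not support that. It answers a different question from the one a collar non-union rate will be taken to answer.

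**Crossover scoring could be left to the analysis plan.** This carries less weight. The article itself fixes the analysis set for all data, the time point, the healing definition and the test, and together these determine the score. No single sentence states it, and the bridging criterion may have been written with the surgical arm in mind. But nothing restricts it to that arm, and nothing counts rescue as failure.

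**Crossovers are reported.** They are, so a reader will see the number of rescues beside the union result. That reduces the risk of being misled but does not give the collar-alone rate.

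**The size is assumed.** This stands in full. The 88% is fracture healing after percutaneous transarticular fixation, not bridging of a grafted posterior fusion. Rescue requires symptoms, and nothing in the article supports a rescued share of 25 to 50%. Power is limited even with no rescue.

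**Counting rescue as failure has its own bias.** Also true. In an open-label trial that hypothesises surgical superiority, the unblinded decision to operate would enter an endpoint now read by a radiologist independent of the study. Some patients fused after the 3-month CT may be delayed unions. The surgical arm has no matching revision rule. A reader might infer that the rescue-as-failure count should replace the CT reading as the sole main result; these points are why that does not follow.

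**Conclusion.** The concern holds in a conditional form. A collar patient fused for symptomatic non-union is counted as healed only if the rescue fusion has bridged on the 1-year CT; a late or failed rescue still counts as non-union. It would be too strong to say that every fused collar patient is scored as healed.

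The direction is certain if any rescue bridges: the counted collar rate then lies below the rate at which the collar alone fails to unite. The size is unknown. Under the illustrative rates the loss is modest when 10% of non-unions are rescued (69% to 59% power at p = 50%, b = 88%) and large from 25% upward, and it is smaller if fewer rescues have bridged by 1 year. These figures rest on an assumed collar non-union rate, rescued share and bridging share, and on a surgical rate borrowed from one small series.

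Union is a secondary endpoint for which no power is stated, and the NDI scoring is not in question. This is a cheap improvement, not a flaw in the trial's main result.

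**What to change.** Add to the Non-union section and to the non-union row of Table 1 an analysis reported beside the as-observed 1-year intention-to-treat result:

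*A patient in either arm who has a fusion or revision for CT-documented non-union or failed fusion before 1 year counts as non-union in the allocated arm, whatever the 1-year CT and flexion-extension films show.*

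In addition:

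- Report fusions for increasing displacement as a separate count.
- State that any claim about union under collar treatment alone rests on the rescue-as-failure analysis, and that the as-observed result describes collar with rescue fusion.
- Leave the rescue rule and the intention-to-treat analysis of the NDI unchanged.

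**Cost.** One analysis sentence and one table row, through the article's usual amendment route. No new visits, scans or reading duties are needed. Crossovers are already documented; what is needed is the reason for each fusion or revision, which can also be classified for patients already treated. Because outcomes are open-label and recruitment began in 2012, the rule should be fixed before the union data are analysed.

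**Downside.** The unblinded decision to operate enters this analysis, and some delayed unions may be counted as non-unions. The as-observed result beside it shows how much this matters.

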#### Surgical treatment

The patient will be surgically treated with an instrumented posterior C1–C2 fusion, including an autologous iliac crest bone graft. The primary fixation technique involves transarticular C1–C2 screws, according to Magerl, and the C1 claw device [20]. In case of anatomical aberrations or a concomitant C1 arch fracture, other techniques may be used: e.g., C1 screws, according to Goel-Harms [21, 22], or translaminar C2 screws, according to Wright [23].

### Study outcome measures

#### Primary outcome measure

The primary outcome variable is the difference in the Neck Disability Index (NDI) at baseline and 1 year after injury [24, 25]. Both comparing differences within the groups (baseline vs. NDI at 1 year), but also differences between the groups. The same evaluation will be made at 6 weeks and 3 months.

#### Secondary outcome measures

EQ-5D scoreKatz ADL (Activities of Daily Living score) at baseline and at 1 yearVisual Analogous Scale (VAS) at baseline and at 1 yearMortalitySerious adverse events (including death) during the first yearRadiographically demonstrable healing on CT after 1 yearUpper cervical stability on dynamic flexion-extension radiographs of the cervical spine after 1 year

